## Abstract

**Background:** Peri-menopausal syndrome (PMPS) has a high incidence rate and seriously affects the physical and mental health of women. Honghua Xiaoyao Pill (HHXYP) is a Chinese patent medicine, which has been reported to be used to treat PMPS. However, there is still a lack of randomized clinical trial to evaluate the efficacy and safety of HHXYP on life quality, mood and vasomotor symptoms for PMPS women. This study aims to investigate whether HHXYP is effective and safe in treating PMPS and the possible mechanism.

**Methods:** A multicenter, randomized, controlled clinical trial will be conducted in China to evaluate the efficacy and safety of HHXYP. Sixty women with peri-menopausal syndrome will be recruited at three centers and randomly in a 1:1 ratio to a treatment group using HHXYP (HHXYP group) and a control group using oryzanol (OC group). Participants will be treated with HHXYP or oryzanol for 12 weeks and followed up for 4 weeks. The primary outcome is the modified Kupperman Index (KI), which will be measured at baseline and 4, 8, 12, 16 weeks after randomization. The secondary outcomes include Hot flash scale (HFs), Menopause-Specific Quality of Life Scale (MENQOL) and Hamilton Depression/Anxiety Scale (HAMD/HAMA). The HFs are measured at the same point as the KI, other secondary outcomes are measured at baseline and 12, 16 weeks after randomization. The other outcomes are the levels of serum sex hormone, monoamine neurotransmitter, vascular vasomotor factor and the expression of phosphatidylinositol 3-active enzyme (PI3K)/protein activator enzyme B (Akt), which will be measured at baseline and 12 weeks after randomization. Adverse events will also be reported.

**Discussion:** HHXYP is a potential alternative Chinese patent medicine for PMPS. This trial will provide evidence for HHXYP on improving the quality of life, mood and vasomotor symptoms, and sex hormone levels of PMPS patients.

## 1 Introduction

Peri-menopause is defined as a period from 2 to 8 years before menopause and 1 year after final menstruation (Speroff, 2002). Nearly all women will experience this period, which is characterized by disturbing symptoms including hot flashes, night sweats, fatigue, insomnia, vaginal dryness and sexual dysfunction, clinically called “peri-menopausal syndrome”. These symptoms results from ovarian dysfunction, which leads to estrogen level fluctuations or reduction, hypothalamic-pituitary-ovarian axis dysfunction, and imbalance of neurotransmitters or hormones. Hot flashes and night sweats are the most frequently reported symptoms, which called as vasomotor symptoms (VMS). In addition, there is evidence to suggest that women during this reproductive transition were more likely to suffer from peri-menopause depression (PMD), leading to a reduced quality of life and increased burden for healthcare needs (Maki et al., 2019).

The conventional treatment for PMPS is hormone replacement therapy (HRT), but many patients refuse to long-term use this treatment because their concern for side-effects such as increased risks of endometrial and breast cancer, stroke, glucose intolerance and thromboembolic disease (Shapiro et al., 2013; Wassertheil-Smoller et al., 2003; Lumsden, 2016; Flores et al., 2021). Standard antidepressants have also been studied as a treatment for both the mood and vasomotor symptoms in peri-menopausal women, but many women are reluctant to use these because of their adverse effect such as weight gain, fatigue and drowsiness (Maki et al., 2018; Maki et al., 2019). Traditional Chinese medicine (TCM) has been widely used for more than 2,000 years to treat PMPS, especially the mood and vasomotor symptoms, with clinical therapeutic effects, safety and low cost.

Honghua Xiaoyao Pill (HHXYP), a Chinese patent medicine, modified from Xiaoyao san (pills), which is used to sooth liver-qi stagnation, activating blood and resolving stasis. It was composed of nine herbal medicines, including Angelica sinensis (Oliv.) Diels [Apiaceae; Angelicae Sinensis Radix], Atractylodes macrocephala Koidz [Asteraceae; Atractylodis Macrocephalae Rhizoma], Carthamus tinctorius L [Asteraceae; Carthami Flos], Paeonia lactiflora Pall [Paeoniaceae; Paeoniae Radix Alba], Poria cocos (Schw.) Wolf [Polyporaceae; Wolfiporia cocos (Schw.) Ryv.&Gibn], Mentha canadensis L [Lamiaceae; Menthae Haplocalycis Herba], Bupleurum chinense Wall. ex DC [Umbelliferae; Bupleuri Radix], Gleditsia sinensis Lam [Fabaceae; Spina Gleditsiae] and Glycyrrhiza uralensis Fisch. ex DC [Leguminosae; Glycyrrhizae Radix et Rhizoma]*.* Mi et al. established an analytical method combining UPLC-Q-TOF/MS and HPLC-QQQ/MS, preliminarily identified 55 components and quantified 14 prototype components of HHXYP (Mi et al., 2020). Another study revealed the key substances of HHXYP therapeutic effect on mammary gland hyperplasia by integrating metabolomics and network pharmacology analysis, including 7 targets, 6 herbs, and 17 ingredients (Gao et al., 2022). Previous study have reported that HHXYP combined with hormone replacement therapy can effectively increase serum estradiol level, reduce KI, MENQOL scores and relieve clinical symptoms of peri-menopausal syndrome (Zhang et al., 2015; Hai et al., 2021). Another study showed that HHXYP combined with Wenjing Decoction can effectively improve the sleep time of patients with peri-menopausal syndrome (Li et al., 2015). However, there is a lack of randomized clinical trials to evaluate the efficacy and safety of HHXYP on life quality, mood and vasomotor symptoms for PMPS women.

In this study, we will carry out a multicenter, randomized, controlled clinical trial to investigate whether HHXYP is effective and safe in treating PMPS. Furthermore, we will evaluate the impact and possible mechanism of HHXYP for life quality, mood and vasomotor symptoms.

## 2 Materials and methods

### 2.1 Study design

This is a multicenter, randomized, controlled trial to investigate the efficacy and safety of HHXYP by comparing with oryzanol. Sixty participants will be included from the following three hospitals: Tongji hospital, Tongji Medical College, Huazhong University of Science and Technology (HUST); Maternal and Child Hospital of Hubei Province, Tongji Medical College, HUST; Wuhan Maternal and Child Health Hospital, Tongji Medical College, HUST. Tongji Hospital is the central structure of the study.

The duration of this study is 17 weeks including screening period of 1 week, treatment period of 12 weeks, and follow-up period of 4 weeks. Informed consent form signed by all qualified participants before enrollment. The Ethics Committee of Tongji Medical College, Huazhong University of Science and Technology approved this trial (approval number:2021S188). The protocol design conformed to the Declaration of Helsinki (Version Edinburgh 2000) and registered on the Chinese Clinical Trial Registry (ChiCTR2100050783). The flow chart of the study has been presented in Figure 1.

**FIGURE 1 F1:**
[figure not shown]
Flow diagram of the trial.

### 2.2 Randomization, allocation concealment and blinding

These participants will be randomly in a 1:1 ratio to HHXYP treatment group and OC group. An independent statistician will use SPSS software to generate the randomization sequence. The designated researcher in the central structure will prepare the assignments in opaque envelopes in sequence, and inform the researcher of the matching card number either by text message or *via* mobile communication application. To ensure blindness in this trial, both of HHXYP and oryzanol pills were packaged with the same appearance throughout the study process, outcome assessors and the data analysts will be blinded to the group allocation.

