#### 2.3.4 Sample sizes

According to a previous study of peri-menopausal women in China (Zhang et al., 2014), we assumed that the mean ± standard deviation (SD) differences in the change in total KI score of the intervention group and the control group were 9 ± 7 and 3 ± 7. PASS 15 software was used for sample size calculation. We determined a sample size of 30 women for each group, with α equal to 0.05 (two-sided) and β equal to 0.01.

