### 2.8 Statistical analysis

All data will be statistically analyzed using SPSS 20.0 software by a special analysts who is blinded to this trial. Continuous variables with normal distribution are presented as mean ± standard deviation (SD), and categorical variables are presented as frequency/percentage. All of the analyses will be performed on intention-to-treat (ITT) principle. Pearson’s chi-squared test or Fisher’s exact test are used to compare the frequency of categorical variables. Non-parametric Mann-Whitney test or Kruskal–Wallis test is used to compare data sets involving non-normal distribution. The comparison of continuous variables between groups will be evaluated by variance analysis. The main outcome scales at different time points will be analyzed by repeated measurement analysis of variance (ANOVA). Significance level is set as *p*-value less than 0.05.

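### Neither the described allocation nor the named analyses use centre, although 60 women come from three hospitals: a loss of precision and exposure to chance site imbalance, not a bias

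*Protocol article*

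**What the plan says.** Section 2.1 of the protocol article describes a multicentre trial: "Sixty participants will be included from the following three hospitals". One of the three is named as the coordinating hospital.

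Section 2.2 sets out the allocation. The ratio is 1:1. On the list it says "An independent statistician will use SPSS software to generate the randomization sequence". On its custody it says "The designated researcher in the central structure will prepare the assignments in opaque envelopes in sequence", and the holder then passes the matching card number to the recruiting researcher. The sequence is in the singular, and neither strata nor blocks are mentioned. On blinding, the section says that "outcome assessors and the data analysts will be blinded to the group allocation".

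Section 2.8 names the analyses. Continuous variables are compared between groups by analysis of variance. For the primary scale, "The main outcome scales at different time points will be analyzed by repeated measurement analysis of variance (ANOVA"). Centre is not named as a factor in either.

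Section 2.3.4 gives the planning values for change in total KI: "intervention group and the control group were 9 ± 7 and 3 ± 7".

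**The concern.** The article gives the ratio, the maker of the list, the software, the holder, the envelopes and the way assignments are relayed. It also names the tests. Centre appears in neither account. Read as written, women from three hospitals draw on one list, and the analysis pools them as if they came from one place.

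Two things follow. First, nothing keeps the arms balanced within a hospital, so with about 20 women per hospital one site may end up with clearly more women on one treatment. If women at that site improve more or less than elsewhere, for instance through a different patient mix, part of that difference enters the one estimate the trial will produce. Second, without a centre term any between-hospital variation in change in KI stays in the residual variance, which widens the confidence interval. In a trial of 60 women both can be reduced at very little cost.

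**Working it through.** **Inputs from the article.** N = 60, three hospitals, 1:1; change in KI 9 v 3, so a planned difference of 6; SD 7 in each arm; 30 per arm; two-sided α = 0.05; β = 0.01.

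**Inputs assumed.** The article gives no per-site numbers and no between-site differences. I take 20 women per site, and vary site sizes and site differences below.

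**Step 1: the plan's own figure.** For β = 0.01, n per arm = 2 × 7² × (1.96 + 2.326)² / 6² = 50.007, rounded up to 51; the t-test also needs 51. So 30 per arm does not give 99% power. A two-sample t-test with 30 per arm has 90.4%. That is a separate matter from this point, but it makes about 90% the reference power here.

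**Step 2: chance imbalance within a site.** Under one list balanced 30:30, the number of HHXYP women among 20 at a site is hypergeometric (60, 30, 20).
- One given site: P(≤ 7 or ≥ 13) = 0.170.
- At least one of three sites, counting all (a, b, c) with a + b + c = 30: 0.353, about 35%. For site sizes 30/20/10 and 40/10/10, the chance that some site has arms differing by 6 or more women is 31% and 24%.
- If the list were simple and unblocked, which the article does not say: one site 0.263, at least one site 1 − (1 − 0.263)³ = 0.60, and an overall split of 36:24 or worse 0.155.

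**Step 3: what imbalance does to the estimate.** Let the three sites differ in mean change by −s, 0, +s KI points (span 2s). With 20 per site the sum of squares is 40s², so the site part of the treatment difference has mean 0 and variance (40s²/59) × (1/30 + 1/30), giving SD = 0.213s. Simulation agrees:

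| Span (KI points) | s | SD of site part | 95% of trials within |
|---|---|---|---|
| 4 | 2 | 0.43 | ± 0.8 |
| 7 | 3.5 | 0.74 | ± 1.4 |
| 10 | 5 | 1.06 | ± 2.0 |

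Unequal site sizes give nearly the same values. The mean estimate stays at about 6.0 with or without centre, and the unadjusted type I error lies between 4.6% and 5.5%, which is 5% within simulation error.

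**Step 4: precision.** What centre is worth depends on what the SD of 7 contains.

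*If 7 includes site variation*, the share removed is (site SD)²/49:
- site SD 2: 4/49 = 8%, residual SD √45 = 6.71, power 93%;
- site SD 3: 9/49 = 18%, residual SD √40 = 6.32, power 95%;
- site SD 4: 16/49 = 33%, residual SD √33 = 5.74, power 98%.

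Power without centre stays near 90%. The three figures above assume balance within sites.

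*If 7 is the within-site SD*, simulated power without centre is 85–87% when sites span 7 points and 80–83% at 10 points; with centre it is 89–90%.

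**Step 5: cost of the factor when sites do not differ.** Two degrees of freedom are lost (58 to 56). Simulated power with centre is 89–90%, against 90–91% without.

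**The case against.** The best reply is that this is a condensed article. Strata, block structure and model covariates are often left to the full protocol or analysis plan, and no sentence says that allocation is unstratified. Envelopes kept in order at one hospital are compatible with a list built in per-centre blocks. This stands in part: a single unstratified list is the natural reading, not a stated fact, and the fix has to be conditional on it. But the article does set out both the mechanism and the analyses, and centre is in neither. The request to model centre does not depend on how the list was built, and if the list is stratified the analysis should reflect that.

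A reader might infer that site and rater differences bias the treatment effect. The documents do not support that. Under randomisation the site contribution averages zero and the type I error holds at 5%. Assessors are stated to be blinded, so ratings should not favour an arm. A rater who is uniformly lenient scores low at baseline as well as later, so most of that effect cancels in change from baseline and in the group-by-time comparison. Only site differences in change matter, and the article reports none.

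A reader might also infer from section 2.9 that scale rating is untrained, because it is not among the training topics named. That list is open-ended, so it does not show this.

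Finally, the realistic shift is modest. If a site's mean change differs from the other two by 3 points and it splits 13:7, the estimate moves by 3 × (13/30 − 7/30) = 0.6 points, against a planned 6. That stands, and it limits the weight of the point.

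**Conclusion.** The point holds as one of efficiency and of protection against accidental imbalance, not of validity. As described, the plan makes no use of centre at either the allocation or the analysis stage, and using it would improve the trial cheaply.

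The size is small to moderate. A notable split in at least one hospital is quite likely, but it moves the estimate materially only if hospitals differ in change in KI by something near 10 points. The precision gain ranges from slight to worthwhile, depending on a between-site SD that nobody has reported. The conclusion rests on the assumed site sizes and site differences, and on the singular wording of section 2.2 meaning one unstratified list. The sponsor can settle the last of these in one sentence. It is a change that should be made, but no reason to doubt the randomised comparison.

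**What to change.** 1. In section 2.2, state whether the list is stratified by centre. If it is not, generate one permuted-block list per hospital, with block sizes that vary and are not disclosed to the sites, for all women not yet randomised. Section 2.10 reports nine women enrolled by 1 June 2022, so at that date most of the 60 could still be covered.
2. In section 2.8, whatever the answer to item 1, add centre as a fixed between-subject factor to the repeated-measures model for KI and to the models for the secondary outcomes. This helps even if the list can no longer be changed.

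Cost: 2 degrees of freedom, and new lists, envelopes and card numbers for the remaining women. Neither item needs additional visits.

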### 2.3 Participants

#### 2.3.1 Recruitment

This study focuses on women experiencing peri-menopausal syndrome. Participants will be recruited from hospitals and local community health service centers. Printed recruitment posters will be distributed in the outpatient of these hospitals and community health service centers. We will also use Internet, WeChat social software to briefly introduce our study to attract potential participants.

#### 2.3.2 Inclusion criteria

Participants are deemed peri-menopause according to STRAW classification (Harlow et al., 2012) and meet the following criteria:1) Health women aged 45–60 years;2) Menstrual disturbance (prolonged menstrual cycle or oligomenorrhea) lasting over 3 months, or amenorrhea for 2–12 months;3) Suffering from vasomotor symptoms (hot flashes, sweating), somatic symptoms (insomnia, fatigue, headache, paresthesia), psychological symptoms (nervousness, melancholia), or urogenital symptoms (dyspareunia, vaginal dryness, urinary infection);4) Serum follicle-stimulating hormone (FSH) > 10 IU/L, or decline of estradiol (E2);5) Peri-menopausal symptoms have not been treated with HRT or other drugs in the last 2 months;6) Uterus and bilateral accessories are complete and without resection;7) Conscious and patients accepted informed consent.

#### 2.3.3 Exclusion criteria

Participants will be excluded from the trial if they meet any of the following criteria:1) Did not meet the above Inclusion criteria;2) Malignant ovarian tumors, ovaries or hysterectomy, premature ovarian failure, hysteromyoma ≥2 cm, and severe hyperplasia of mammary glands;3) Acute gynecological infectious diseases or other acute infectious diseases;4) Severe liver and kidney dysfunction, or other severe system diseases;5) Use hormone drugs or Chinese medicine for treatment in the last 2 months;6) have participated in other clinical trials;7) Patients who failed to receive treatment as required or withdrew from the trial.

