### 2.7 Safety outcomes

In order to exclude serious heart, liver, and kidney diseases, all participants will also receive urine, stool, blood routine, liver function (ALT, AST), kidney function (BUN, creatinine) and ECG examination before and after treatment. Participants will inform the researchers adverse events or uncomfortable symptoms by WeChat software, telephone, or short message. Adverse events should be recorded in the Case Report Form and resolved immediately. Serious adverse events should be reported immediately to the principal investigator. The details of outcome assessment chart is given in Table 1.

**TABLE 1 T1:** Trial processes chart.

Period	Enrollment	Baseline	Treatment			Follow-up
Time points	Week -1	Week 0	Week 4	Week 8	Week 12	Week 16
Patients						
Medical history	√					
Physical examination	√				√	
Laboratory examination	√				√	
Informed consent	√					
Randomization	√					
Intervention						
HongHua XiaoYao Pills (HHXYP) group			0.39g/pill, 2 pills, three times daily			
Oryzanol Control (OC) group			10mg/pill, 2 pills, three times daily			
Outcomes						
the modified Kupperman Index (KI)	√	√	√	√	√	√
Hot flash scale (HFs)	√	√	√	√	√	√
MENQOL		√			√	√
HAMD		√			√	√
HAMA		√			√	√
Serum E2, FSH and LH levels		√			√	
Serum NE, 5-HT and DA levels		√			√	
Serum NO, ET-1 and CGRP levels		√			√	
Expression of PI3K, Akt, and pAkt		√			√	
Trial evaluation						
Safety of medicine			√	√	√	√
Adverse event			√	√	√	√
Reasons of drop-outs or withdrawals			√	√	√	
Patient’s compliance					√	

E2, estradiol; FSH, follicle-stimulating hormone; LH, luteinizing hormone; NO, nitric oxide; ET-1, endothelin-1; CGRP, calcitonin gene-related peptide; NE, norepinephrine; 5-HT, serotonin; DA, dopamine; PI3K, phosphatidylinositol 3-active enzyme; Akt, protein activator enzyme B; pAkt, phosphorylated protein kinase B.

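### Exclusion criterion 7 takes non-adherent and withdrawn women out of the trial, mostly after randomisation, which contradicts the stated ITT analysis and can bias the comparison

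*Protocol article*

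**What the plan says.** Section 2.3.3 opens its list with "Participants will be excluded from the trial if they meet any of the following criteria", and item 7 of that list is "Patients who failed to receive treatment as required or withdrew from the trial". On the analysis population, section 2.8 states: "All of the analyses will be performed on intention-to-treat (ITT) principle". No per-protocol, completer or other analysis set is named anywhere in the article.

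On timing, the Abstract says "Participants will be treated with HHXYP or oryzanol for 12 weeks and followed up for 4 weeks". Table 1 places consent and randomisation together in the enrolment column (Week -1), ahead of the treatment visits at Weeks 4, 8 and 12 and the follow-up visit at Week 16. KI, the primary outcome, is scheduled through Week 16 (section 2.5.1).

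**The concern.** An eligibility criterion has to be decidable before allocation. Item 7 describes conduct that is mostly seen only afterwards, so it cannot screen women in or out. In practice it can only remove women who already belong to a randomised arm. Analysis by ITT requires the opposite: each randomised woman is compared in the group to which she was assigned, whether or not she took the treatment or stayed to the end.

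In a symptom trial, stopping treatment may be tied to lack of benefit or to side effects, and either can differ between HHXYP and oryzanol. The women left after such removal would then no longer be a randomised comparison, and an apparent effect could be created or hidden. If a site reads item 7 as the end of participation and collects no further KI scores, a later ITT statement cannot recover them.

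**Working it through.** **1. The two statements side by side**

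| Woman | Section 2.3.3, item 7 | Section 2.8 |
|---|---|---|
| Randomised, does not take treatment as required | Excluded from the trial | Analysed as allocated |
| Randomised, later withdraws | Excluded from the trial | Analysed as allocated |
| Consents, withdraws before allocation | Excluded from the trial | Not randomised, so no conflict |

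Only the third row is free of conflict. It covers a narrow window, because Table 1 puts consent and randomisation in the same column.

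**2. Inputs for sizing a possible bias**

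- From section 2.3.4: mean KI changes and SDs for "the intervention group and the control group were 9 ± 7 and 3 ± 7", so the planned difference is 9 − 3 = 6 and the SD is 7; 30 women per group.
- Not in the article, and therefore assumed: the proportion excluded in each arm (d₁, d₀), and the gap g by which excluded women improve less than those kept.

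The article states no figure for exclusions, so there is none to reproduce. (The planned 30 per group does not reproduce at the printed β of 0.01, which needs 51 per group; it does at β of 0.10. That is a separate matter and does not enter here.)

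**3. Differential exclusion, no true effect**

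If a fraction d is excluded and the gap is g, the overall mean is the kept mean minus d·g, so the kept mean is too high by d·g. The shift in the group difference is (d₁ − d₀)·g. With SD held at 7 among women kept, SE = 7·√(1/n₁ + 1/n₀), and the two-sided type I error is 1 − Φ(1.96 − shift/SE) + Φ(−1.96 − shift/SE).

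| Excluded, arm 1 vs arm 0 | Kept | SE | Gap g | Shift | Type I error |
|---|---|---|---|---|---|
| 10% vs 10% | 27, 27 | 1.91 | 3 or 6 | 0 | 5.0% |
| 20% vs 20% | 24, 24 | 2.02 | 3 or 6 | 0 | 5.0% |
| 20% vs 10% | 24, 27 | 1.96 | 3 | 0.10 × 3 = 0.3 | 5.3% |
| 20% vs 10% | 24, 27 | 1.96 | 6 | 0.10 × 6 = 0.6 | 6.1% |
| 30% vs 10% | 21, 27 | 2.04 | 3 | 0.20 × 3 = 0.6 | 6.0% |
| 30% vs 10% | 21, 27 | 2.04 | 6 | 0.20 × 6 = 1.2 | 9.1% |

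Against the planned 6 points, these shifts are 0.3/6 = 5% to 1.2/6 = 20%. The sign follows the arm with more exclusions: more in the HHXYP arm favours HHXYP, more in the oryzanol arm favours oryzanol.

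**4. Upper bound**

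Suppose exactly the worst-responding fraction q of one arm is removed and nobody from the other. For a normal outcome the kept mean rises by SD·φ(z_q)/(1 − q):

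- q = 0.10: 7 × 0.1755/0.90 = 1.36 points
- q = 0.15: 7 × 0.2332/0.85 = 1.92 points
- q = 0.20: 7 × 0.2800/0.80 = 2.45 points

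No other pattern of exclusion at the same rate can raise that arm's mean further.

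**The case against.** The strongest reply is that item 7 is a discontinuation rule printed in the wrong list. Section 2.3.3 is about taking part in the trial and says nothing of analysis sets. The only sentence on who is analysed is the ITT one, and Table 1 has a row for "Reasons of drop-outs or withdrawals", so withdrawals are expected and recorded. This is plausible. It does not remove the conflict, because the text as it stands excludes these women and nothing says they stay in the analysis. It also leads to the same correction. Nor is this a detail that a condensed article leaves to another document: two printed statements disagree.

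Several stronger readings are tempting, and the documents do not support them:

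- *The primary analysis will be a completer or per-protocol analysis.* No such set is named. This would follow only if item 7 overrides section 2.8, which the article does not say.
- *The comparison is biased.* Bias is possible, not shown. There are no exclusion rates and no information on who would be excluded in each arm.
- *The bias is about 2.4 points, or some 40% of the planned difference.* That is the extreme of step 4 (2.45/6), with perfectly selective removal from one arm and none from the other.
- *The exclusions cost a known amount of power.* That needs an assumed, unselective loss in both arms with the 6-point difference intact, which is a different scenario from selective exclusion.
- *Table 1 shows the same fault because its drop-out row has no Week 16 entry.* That is a scheduling matter and says nothing about who is analysed.

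It also stands that some withdrawals can precede allocation, so not every case under item 7 arises after randomisation.

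**Conclusion.** The contradiction between section 2.3.3, item 7, and section 2.8 is real and rests on the text alone. Taken literally, item 7 removes randomised women whom the ITT principle keeps.

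The consequence is conditional. Bias arises only if the item is applied, exclusion is related to outcome, and that relation or the exclusion rate differs between arms. The moderate scenarios in step 3 put it at a fraction of a point to just over one KI point; step 4 gives the ceiling for exclusion of up to 20% from one arm. All these sizes rest on assumed exclusion rates and, in step 3, on an assumed gap and an unchanged SD of 7. None is a forecast for this trial.

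**What to change.** - Remove item 7 from the exclusion criteria in section 2.3.3, and record such cases as treatment discontinuation or withdrawal from the trial.
- State that the scheduled KI assessments are sought through Week 16 for women who stop treatment, where their consent allows.
- State in section 2.8 that every randomised woman is analysed in her assigned group, and that any exclusion for non-adherence is confined to a per-protocol sensitivity analysis labelled as such.

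The cost is a short protocol amendment and continued contact with women who stop treatment. No stated figure changes: the planned 30 per group remain the analysed groups. Section 2.10 reports nine women enrolled by 1 June 2022, so recruitment was still at an early stage when the article was written.
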